##### The intervention group (the O2O-PEP mini-app)

The O2O-PEP mini-app is the primary user-oriented platform for the intervention group. Following randomization, intervention group participants are directed to the gamification-based PEP education package, with a link to make online bookings anonymously available on the screen whenever participants want to click during the gamification procedure. After successful online booking, clients present their PEP prescription requisition e-ticket to the clinical doctor in the study-selected hospital, the clinical doctor will start the PEP regimen according to the Chinese national guideline, and the nurse in the same department will conduct essential PEP counseling when requested by participants. Participants will not be permitted to share the study advertisement with others. To restrict access to the min-app to intervention group participants only, those randomized into the intervention group will be provided a single-use verification code which will be entered to gain access to the intervention. Participants will have unlimited access to the mini-app after randomization until the end of the study.

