##### The control group (routine PEP-related care)

Participants in the control group would not be directed to the O2O-PEP mini-app after randomization, but will receive HIV- and PEP-related services following the current practices in health care services, including electronic HIV prevention materials, referrals to local PEP services, and a standard procedure to access PEP through the study hospital.

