**Primary outcomes**					
Acceptability	System usability scale (30)		√		√
Feasibility	Exposure time to the mini-app		√		√
PEP initiation	PEP initiation during study time	√	√	√	√

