**Laboratory testing**					
HIV Ag/Ab testing	HIV-1/2	√	√	√	√
Syphilis	Syphilis serology	√	√		√
Gonorrhea/ Chlamydia	first-catch urine, oral, urethral, and rectal mucosal secretions	√	√		
HBV	HBsAg, anti-HBs, anti-HBc	√			√
HCV	HCV antibody test	√			√
Serum creatinine	Kidney function test	√	√		
ALT, AST	Liver function test	√	√		

The primary efficacy outcome is PEP initiation. PEP initiation data will be collected through the clinical records in the study hospitals, which is a binary variable (1 = PEP initiation during the study period, otherwise 0). The acceptability outcome will be measured by the System Usability Scale (SUS) (30). For feasibility, we will assess the cumulative exposure time to the mini-app, as well as time spent on specific components of the mini-app, which will be automatically collected by participant application log files.

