##### Statistical analysis plan

All statistical analyses will be conducted using SAS software (version 9.4, SAS Institute, Inc. USA), with a two-sided *p*-value of <0.05 considered statistically significant. The primary analysis will be performed by intention-to-treat analysis. Descriptive statistical analysis will be first carried out to report baseline demographics, outcome variables, and other covariates at different follow-up time points, and then compared with Chi-square/Fisher exact probability tests (for categorical variables) or *t*-test/Mann Whitney U test (for continuous variables) between those who finish follow-ups and those who do not and between the mini-app group and the control group.

The preliminary efficacy of the min-app intervention to increase PEP initiation (any PEP initiation over follow-ups) will be evaluated using an unadjusted risk ratio. As for model acceptability, point estimates for a SUS score of ≥50 will be considered the minimum criteria for acceptability. Descriptive analysis will be used to evaluate model usability, including cumulative time to the mini-app, and time spent on specific components of the mini-app. Multiple imputations will replace missing data, and a sensitivity analysis will be performed to compare the multiple imputation analysis with the full case analysis.

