## Discussion

The HIV epidemic among MSM is spreading worldwide (50). Thus, promoting the O2O model application in scaling up biomedical HIV prevention interventions (e.g., PrEP and PEP) is essential. Our study aims to design the O2O-PEP model and evaluate its efficacy in promoting PEP uptake with a stratified RCT design among Chinese MSM. We propose that this O2O-PEP model will also provide opportunities for further HIV interventions (e.g., the transformation from PEP to PrEP).

Our model consists of three innovative components. First, the gamification-based PEP education packages provide a more entertaining format in the context of behavioral education, which has been adopted in other HIV interventions, such as HIV testing and shame reduction in MSM (28, 51). Second, the online HIV risk assessment tools can improve individual risk awareness and subsequent PEP-seeking actions. Third, the online booking system promotes PEP service accessibility. Furthermore, as PEP must be started within 72 h after a potential exposure to HIV, every effort should be made to provide timely PEP as soon as possible after suspicious exposure. The potential of the O2O model to deliver prompt response and dramatically reduce the linkage time makes it an ideal PEP service delivery solution.

There may be several potential challenges to the success of our study. First, the proportion of MSM being transferred from online to offline PEP prescription may be low, as PEP is relatively expensive and uncovered by Medicare in China. We try to use program funds to subsidize part of drug and laboratory test costs; second, compared with modern industrial games, the gamification-based design in our study is slow to update, which may cause study participants to lose interest. To keep participants engaged in the study, we will build in frequent releases of improved gamification content. Third, the sample size we used for primary efficacy evaluation was relatively small, and further large sample implementation studies are needed.

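### Imputing SUS for O2O-PEP men who never opened the app, with a full-case check that also rests only on raters, leaves non-use out of the acceptability outcome

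*Protocol article*

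**What the plan says.** Table 1 of the protocol article lists SUS (acceptability) and "Exposure time to the mini-app" (feasibility) as primary outcomes at months 1 and 6, next to PEP initiation. Neither row names an arm.

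Only the intervention arm can reach the app. Those men receive a "single-use verification code which will be entered to gain access to the intervention", and the control-group section states: "Participants in the control group would not be directed to the O2O-PEP mini-app after randomization".

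Exposure time and time per component come from the app itself, "which will be automatically collected by participant application log files" (Outcomes and covariates of the study, text after Table 1).

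The Statistical analysis plan section sets an intention-to-treat primary analysis. It compares outcome variables between the two groups without exempting the two app-only outcomes, and describes exposure time descriptively. Its acceptability rule is that "point estimates for a SUS score of ≥50 will be considered the minimum criteria for acceptability". Its one sentence on missing data is: "Multiple imputations will replace missing data, and a sensitivity analysis will be performed to compare the multiple imputation analysis with the full case analysis". That sentence names no outcome, arm or reason for missingness, and exempts none.

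**The concern.** SUS asks a person to rate a product. A man who never entered his code has nothing to rate, so his score is undefined, which is different from a score that exists but was not collected. Multiple imputation is meant for the second case. Applied to the first, it gives him a usability rating modelled on men who used the app.

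The planned sensitivity analysis does not expose this. A full-case analysis drops men without a score, so it too describes only raters. Agreement between the two analyses would say nothing about how many men in the arm never used the app.

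Acceptability is among the pilot's stated purposes, and SUS of at least 50 is its only stated acceptability threshold. The Discussion also expects some disengagement: "the gamification-based design in our study is slow to update, which may cause study participants to lose interest". If many men ignore the app and the rest like it, the acceptability result as planned would look the same as if everyone had used it.

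**Working it through.** The plan gives no figure on this point to reproduce. The check has two parts: what each rule does to each kind of man, and an illustration of size.

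**1. Rules against cases**

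| Man | SUS | Exposure time | Effect of the stated rule |
|---|---|---|---|
| O2O-PEP, uses app, answers survey | observed | observed | none |
| O2O-PEP, stops using app, answers survey | observed, from experience | observed total | none |
| O2O-PEP, opened app, skips survey | missing | observed total | SUS imputed; dropped in full case |
| O2O-PEP, never opens app | does not exist | 0 | SUS imputed from users; dropped in full case |
| Control | not applicable | not applicable | not stated; arm restriction unwritten |

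The fourth row is the core of the problem. The third row is ordinary non-response: imputation can be argued for there, although not rating may itself carry information.

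**2. Size, on assumed values**

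Inputs:
- O2O-PEP arm size: 25 (Sample size section).
- Number of never-openers, *k*: not in the documents; taken as 3, 5 and 10.
- Share of users with SUS of at least 50, *q*: not in the documents; taken as 80%.
- Every man who opens the app is taken to give a rating.

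Imputation from users: the expected share over the arm is [*q*(25 − *k*) + *qk*]/25 = *q*, so about 80% whatever *k* is. Full case: *q* again, 80%.

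Never-openers counted as not meeting the criterion: *q*(25 − *k*)/25.

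- *k* = 3: 0.80 × 22/25 = 70.4%, a gap of 9.6 points.
- *k* = 5: 0.80 × 20/25 = 64.0%, a gap of 16 points.
- *k* = 10: 0.80 × 15/25 = 48.0%, a gap of 32 points.

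If the criterion is read as a mean score, the same thing happens. Imputation from users leaves the expected mean at the users' mean for any *k*.

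**3. Exposure time**

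With an assumed user mean of 60 minutes and zeros kept, the arm mean is 60 × (25 − *k*)/25, which is 52.8, 48.0 and 36.0 minutes for *k* = 3, 5 and 10. An overstatement, by 25/(25 − *k*) = 1.14, 1.25 and 1.67, would arise only if a never-opener's absent log were treated as missing and then imputed. The protocol does not say that.

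**The case against.** The strongest reply is that this is a condensed article. The imputation sentence is general, names neither SUS nor exposure time, and an analysis plan not shown may specify the imputation model and its exceptions. Never-opening may also be uncommon: participants are guided automatically to their allocated link after randomization, and intervention men are sent straight to the education package. Follow-up surveys carry a reminder and a payment. A comparison of those who finish follow-up with those who do not is also planned, and could show lower app use among non-finishers.

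Much of this stands as a limit on size, since no rate of non-use can be read from the documents. It does not remove the point. The article states a missing-data rule and its check, and as written they do not fit a primary outcome. The finisher comparison would not change the SUS estimate, and a never-opener who completes his surveys counts as a finisher.

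A reader might infer more, and the documents do not support it:

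- **That exposure time is biased too.** It comes from automatic logs. A never-opener has zero and a man who stops has an observed total.
- **That men who stop using the app cannot give a SUS score.** They can; the score is missing only if they skip the survey.
- **That control values would be imputed.** Nothing says so. The gap is only that the arm restriction is unwritten.
- **That the pilot expects 10% loss.** That figure belongs to the calculation for about 400 participants; no attrition rate is stated for the 50-person pilot.
- **That a chance of wrongly passing the SUS threshold can be quoted.** It would need a SUS mean, a standard deviation and a non-rater mean, and the documents give none of these.

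**Conclusion.** The point holds for SUS. Read as written, the Statistical analysis plan section estimates acceptability as though never-openers in the O2O-PEP arm had used the app, and its sensitivity analysis cannot show otherwise.

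The size is not known. The 70%, 64% and 48% against 80% are illustrations resting on an assumed 80% among users, assumed counts of never-openers, a rating from every man who opened the app, and imputation that reproduces the users' distribution. If every O2O-PEP man opens the app, the never-opener problem disappears and only ordinary survey non-response remains.

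For exposure time the finding is limited to clarity: there is no bias if logged zeros are used as recorded. The correction is worth making before analysis because it affects what the pilot can conclude about acceptability.

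**What to change.** In the Statistical analysis plan section:

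1. State that SUS and exposure time are analysed in the O2O-PEP arm only, and leave them out of the between-arm comparison of outcomes.
2. Do not impute SUS for men who never opened the app. Report SUS among raters, always with the number who opened the app and the number who rated it, out of all randomized to O2O-PEP.
3. Add a sensitivity analysis giving the proportion of the whole O2O-PEP arm with SUS of at least 50. Count never-openers as not meeting it and, as a conservative bound, non-raters as well. A proportion is used because no whole-arm mean exists when some men have no score. It stands beside the existing criterion and adds no new threshold.
4. State that a never-opener's exposure time is an observed 0, not a missing value.

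Multiple imputation can stay for the survey scales that both arms can answer.

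The cost is wording and one small descriptive table from logs and surveys already planned, with no extra participants or visits. The downsides are a less favourable acceptability figure and a conservative bound that also counts men lost for unrelated reasons; the bound should be labelled as such.

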##### Follow-ups

Follow-ups will be conducted at 1, 3, and 6- months after randomization. In each follow-up, participants are invited to complete a survey relating to social support, HIV health literacy, HIV risk perception, sexual and HIV risk behaviors, mental health, and PEP uptake. Each participant will be compensated 50 RMB (the currency of China), or ~$ 8. After 1 week, participants who do not respond to the investigation will be sent a reminder offering them one additional week for completion.

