##### Sample size

Our previous study found that ~5% of MSM self-reported using PEP before the survey (36). A sample of ~400 participants (200 per group) would achieve 90% power to detect a moderate effect corresponding to a difference of at least 9% points (equivalent to a relative risk of 2.8 assuming a 5% prevalence of PEP usage in the control group) in PEP uptake between the intervention and control groups using a two-sided test at a 5% significance level and assuming a 10% attribution rate after 6 months. According to Cocks et al. (37) the sample size of a pilot trial should be at least 9% of that of the main planned trial. Hence, we plan to recruit 50 participants, 25 per group, to assess preliminary evidence for the further main study.

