## Ethics statement

This study was approved by the medical institutional review board (IRB) of Binzhou Medical University (IRB No. 2021-007). All participants will sign an electronic informed consent form before enrolling in the study, which will also authorize access to their clinical records in the study hospitals. Each participant will be compensated 50 RMB each for completion of the baseline, 1, 3, and 6-month follow-ups. If the intervention proves to be effective, access to the invention is guaranteed for all high-risk MSMs even after the study has been concluded. We would also share the implementation challenges and successes in future research by reporting on international conferences and peer-reviewed articles.

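### The imputation versus full-case comparison cannot test the record-based primary outcome, while PEP obtained outside the study hospitals is coded 0 and left untested

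*Protocol article*

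**What the plan says.** **Outcome.** Under Outcomes and covariates of the study, in the text below Table 1, the article states that "PEP initiation data will be collected through the clinical records in the study hospitals". Its coding rule for the outcome reads: "which is a binary variable (1 = PEP initiation during the study period, otherwise 0". The Ethics statement adds that all participants sign a consent form "which will also authorize access to their clinical records in the study hospitals".

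**Analysis.** The Statistical analysis plan section says "The primary analysis will be performed by intention-to-treat analysis" and that "PEP initiation (any PEP initiation over follow-ups) will be evaluated using an unadjusted risk ratio". On missing data it says "Multiple imputations will replace missing data, and a sensitivity analysis will be performed to compare the multiple imputation analysis with the full case analysis". The article names no other sensitivity analysis.

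**Where PEP can be obtained.** The intervention group section routes mini-app bookings to the study-selected hospital. The control group section gives controls referrals to local PEP services, and also a standard route to PEP through the study hospital.

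**Other data on PEP use.** The 1-, 3- and 6-month surveys cover "social support, HIV health literacy, HIV risk perception, sexual and HIV risk behaviors, mental health, and PEP uptake".

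**The concern.** A sensitivity analysis should probe the assumption most likely to be wrong. Here the outcome is defined so that missingness cannot arise through survey non-response, yet the only named check concerns missingness. The assumption that carries the weight is a different one: that no record in a study hospital means no PEP. A man who starts PEP elsewhere is a true initiator counted as a non-initiator.

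If this happens equally often, in relative terms, in both arms, it cancels from a risk ratio. The two arms are not directed alike, however. The mini-app steers its users to the place where the outcome is counted, and controls are also pointed to services where it is not. Some of an apparent effect could then be a change in where men obtain PEP, not in whether they obtain it. The pilot is meant to supply preliminary evidence for a main trial, so this distinction matters for what is carried forward.

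**Working it through.** **1. Inputs and the plan's own figures (Sample size).** Control rate 5%, difference 9 points, so 14% with the mini-app; 0.14/0.05 = 2.8, which agrees with the stated relative risk. The pilot has 25 per group. I read the 10% allowance after 6 months as attrition: 0.10 × 50 = 5 men.

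The article also states: "A sample of ~400 participants (200 per group) would achieve 90% power". The usual formula is n = [z(α/2)·√(2p̄(1−p̄)) + z(β)·√(p1(1−p1) + p2(1−p2))]² / (p2−p1)². With p̄ = 0.095 and a two-sided 5% test it gives [1.960 × 0.4147 + 1.282 × 0.4098]² / 0.0081, or 221 per group. That is 442 in total, and 442/0.9 = 492 after attrition. A one-sided 5% test gives 180 per group and 360/0.9 = 400. The stated 400 therefore does not reproduce with the stated two-sided test. That is a separate matter, and nothing below depends on it.

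**2. Can PEP initiation be missing?** By definition, the value is 1 if a study-hospital record shows initiation and 0 otherwise.

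- Missing values among 50 randomised: 0.
- Values imputed: 0.
- Full-case set for an unadjusted risk ratio, which needs no survey covariate: 25 versus 25.

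Illustration with counts near the planned rates: 3/25 versus 1/25 gives 0.12/0.04 = 3.0 under intention-to-treat, under imputation and under full case. The three agree by construction, so their agreement is not evidence of robustness.

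**3. Text that points the other way.** The sample size allows for attrition on PEP uptake, although losing contact with a man loses no record-based outcome. Table 1 schedules PEP initiation at the follow-up visits. The analysis section counts initiation over follow-ups, where the outcome definition says during the study period. If an analyst treated survey dropouts as missing (the text does not say this), and if all 5 were non-initiators, the full-case result in the example would depend on the split between intervention and control:

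| Dropouts (intervention/control) | Full-case RR |
|---|---|
| 5/0 | (3/20)/(1/25) = 3.75 |
| 3/2 | (3/22)/(1/23) = 3.14 |
| 2/3 | (3/23)/(1/22) = 2.87 |
| 0/5 | (3/25)/(1/20) = 2.40 |

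The reading chosen therefore changes the estimate.

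**4. Off-site PEP.** Let c_I and c_C be the shares of true initiations that reach study-hospital records in the intervention and control arms. Then RR(recorded) = RR(true) × c_I/c_C. Equal shares leave the ratio unbiased, and c_C below c_I inflates it. Starting from recorded counts of 3/25 versus 1/25:

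| Off-site initiations added | Counts | RR |
|---|---|---|
| none | 3/25 vs 1/25 | 3.0 |
| one control | 3/25 vs 2/25 | 1.5 |
| one in each arm | 4/25 vs 2/25 | 2.0 |
| one intervention | 4/25 vs 1/25 | 4.0 |

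The second row corresponds to c_I = 1 and c_C = 1/2.

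**5. Why one event matters.** Expected events are 25 × 0.05 = 1.25 in controls and 25 × 0.14 = 3.5 with the mini-app. The chance of no control event at all is 0.95^25 = 0.28.

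**The case against.** A reader might infer something stronger: that the imputation rule overwrites known zeros, that the full-case analysis discards men with known outcomes, and that intention-to-treat is broken. The documents do not support this. A rule that replaces missing data leaves recorded values alone. Full case is only a sensitivity comparison, and the primary analysis is stated to be intention-to-treat. The rule also has a proper object in the survey scales (SUS, PEP knowledge, PHQ-9, anxiety and the Levesque constructs). Nor does the text propose imputing SUS or app time for controls, for whom they do not apply. Which variables enter the imputation is detail an article may leave to the full plan.

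Two further objections carry weight. First, off-site PEP is a question of outcome ascertainment, and the imputation sentence is not itself wrong. That is correct. The point is that the named check does not reach the outcome it would be expected to test. Second, the size and direction of the bias are unknown. Controls also have a route through the study hospital, and mini-app users may go elsewhere. In so small a pilot, RR 3.0 from 3 versus 1 events has an approximate 95% interval of 0.33 to 27, from exp(ln 3 ± 1.96·√(1/3 − 1/25 + 1/1 − 1/25)). RR 1.5 lies well inside it, so no significance statement would change. This limits the weight of the point but does not remove it, since sampling error does not excuse a bias that the planned surveys could examine.

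**Conclusion.** The concern holds in a limited form. As defined, PEP initiation is complete for all 50 men, and comparing imputation with full-case results says nothing about it. The attrition allowance and the wording about follow-ups leave room for a second reading that should be closed. The untested weakness is PEP from outside the two study hospitals being coded 0. The different referral routes make it plausible that this favours the intervention. In the illustration one such control event halves the risk ratio, from 3.0 to 1.5.

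This rests on three assumptions: study-hospital records can be consulted and matched for every randomised man; consent to record access is not withdrawn; and some off-site initiation occurs. The article gives no figure for the last, so the example shows sensitivity and is not an estimate of bias.

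**What to change.** - State that PEP initiation is analysed from study-hospital records for all randomised participants, whether or not they answer the surveys. Use one description of the time window in the outcome definition, Table 1 and the analysis section, and say what the attrition allowance is for.
- Keep multiple imputation, and its comparison with full cases, for the survey scales.
- Make the sensitivity analysis of the primary outcome one in which a man counts as an initiator if either the hospital record or any 1-, 3- or 6-month survey shows PEP started after randomisation. Report it by arm next to the record-based result.

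The cost is a few sentences and no new data, because the surveys already ask about PEP uptake. Self-report is open to recall and reporting bias and to survey non-response, so it should stay a sensitivity analysis and not replace the record-based outcome.
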